### Inclusion criteria

(1) Age 18 years or older(2) Time of admission to the ICU ≥ 24 h and diagnosis of SAP complicated with ARDS within 48 h of admission to the ICU

AP diagnosis requires two of the following three items: (1) persistent upper abdominal pain; (2) serum lipase and (or amylase) concentrations at least three times greater than the upper limit of normal; and (3) abdominal imaging test results show imaging changes consistent with AP.

SAP was diagnosed based on the revised Atlanta classification (RAC) in 2012 [26]. SAP is defined as persistent organ failure > 48 h. Organ failure is diagnosed as an organ score ≥ 2 for one of three organ systems based on the modified Marshall scoring system.

Diagnosis of acute respiratory distress (ARDS) syndrome was based on the Berlin criteria for acute respiratory distress syndrome. The required criteria must have all four of the following: (1) within 1 week of a known clinical insult or new or worsening respiratory symptoms; (2) chest imaging showing bilateral opacities not fully explained by effusions, lobar/lung collapse, or nodules; (3) respiratory failure is not fully explained by cardiac failure or fluid overload, need objective assessment (e.g., echocardiography) to exclude hydrostatic edema if no risk factor is present; and (4) oxygenation index (PaO_2_/FiO_2_) ≤ 300 mmHg under positive end-expiratory pressure (PEEP) or continuous positive airway pressure (CPAP) ≥ 5 cmH_2_O [27].(3) Signed informed consent.(4) Participant who voluntarily received this experimental treatment and completed the course of treatment.

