### Exclusion criteria

(1) Unable to walk independently before onset(2) Cognitive dysfunction before onset(3) Previous neuromuscular disorders (e.g., severe muscular atrophy, amyotrophic lateral sclerosis, myasthenia gravis, etc.)(4) Severe fractures, spinal cord injury, deep vein thrombosis, etc., need to be stopped(5) The onset time was ≥ 7 days, and the treatment was completed in the ICU of another hospital(6) Pregnancy(7) When the patient has a pacemaker(8) Death within 24 h(9) End-stage malignant tumor(10) The patient or his authorized client refused to participate in this study

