### Participant recruitment

Patients meeting the eligibility criteria will be screened from the Department of Critical Care Medicine, the Second Affiliated Hospital of Chongqing Medical University. The recruitment period will be April 2023–April 2025. To screen SAP patients with ARDS, a physician in critical care medicine will complete the clinical diagnosis within 48 h of the patient’s admission and then will refer them to a physical therapist to assess whether the patient would be eligible to participate in this trial. Eligible patients will be randomly divided into the NEMS group or control group by an investigator. Baseline assessment will be completed after signing the informed consent form. Considering the risk of muscle wasting in the early stage of bed rest, patients will be given corresponding intervention immediately after participating in the trial. Investigators will check the list of eligible patients daily to determine whether the patients completed the assessment and intervention of the trial process. In addition, investigators will be responsible for maintaining long-term contact with patients and communicating about patient recovery, improving patient adherence, and reducing the failure rate of follow-up.

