#### NMES group intervention

NMES intervention will be performed on the first day of patient enrollment, and the intervention will continue for 7 days (Fig. 2). During the intervention, patients will take a supine position with the head elevated 30°, and the position of both lower limbs will be 15° hip flexion and 30° knee flexion to achieve the best muscle contraction [28]. Four groups of self-adhesive electrodes (5 cm × 5 cm) will be placed on motor points (rectus femoris, anterior tibial). The NMES intervention will be designed 60 min/day, including a 5-min warm-up, 50-min stimulation sessions, and a 5-min cooldown. The stimulation frequency of warm-up is 4 Hz, and the intensity will gradually increase to achieve visible contractions. Fifty-minute stimulation sessions consisted of 10 s of contraction stimulation (pulse width = 300 μs, frequency = 45 Hz), and the stimulation intensity met maximum muscle contraction without causing discomfort. In addition, a 5-s rest phase with a 4-Hz stimulation frequency will be performed. Cooldown sessions (frequency = 45 Hz) are composed of gradually decreasing intensity. During whole intervention sessions, intensity will be increased to avoid tissue accommodation. The physiotherapist will monitor the intervention period to prevent adverse reactions. In addition, NMES participants will receive routine care during the 7-day NMES intervention.

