### Control group intervention

The control group will not receive NMES treatment. Routine care for the control group guided by treating clinicians, including health education, suction, regular turnover per 2 h, and elevating the head of the bed, will be completed by nurses. Early physiotherapy will be provided by physiotherapists. Patients who are unable to cooperate with sedation therapy will receive passive range-of-motion exercises. Responsive patients will be encouraged to receive out-of-bed mobilization and active exercise therapy (strength training, balance, standing, and walking). Early physiotherapy will be delivered according to physiotherapy intervention recommendations [29].

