### Data collection and statistical analysis

Two trained evaluators will collect baseline data, outcomes, and follow-up data. Participant trial data will be recorded through the case report form. Participants will be informed of follow-up visits after discharge from the hospital, and follow-up data will be obtained through telephone questionnaires or home visits. Two investigators will check the case report form twice to ensure accuracy and completion and record the data of the case report form into the Excel file with double-check.

All participants can withdraw from the trial at any time. If participants terminate the trial or deviate from the intervention protocol, the investigators will record the trial data from the participant’s last intervention and report the reason for withdrawal.

The SPSS 26.0 software (IBM SPSS, Chicago, IL) was applied to analyze the baseline characteristics and outcomes between the two groups. *x̅* ± s will represent continuous variables that conformed to the normal distribution, and the *t* test will compare the differences between the two groups. The Mann–Whitney *U* test will be applied if continuous variables are not normally distributed. Categorical variables will be expressed as frequency (percentage, %), and the chi-square test will be used to compare the differences between the two groups. Effect estimates will be provided with corresponding 95% confidence intervals, and *P* values ≤ 0.05 will be considered significant. Aiming to preserve the unique benefit of randomization, regardless of whether that participant received the allocated intervention, the principles of intention-to-treat analysis will be used. All randomized participants will be included in the analyses, and data will be analyzed in the group in which the participants were originally randomized. All available data from the NMES group that was originally randomized will be analyzed as an intervention group, including participants from the NMES group who do not complete the NMES intervention or even do not receive NMES intervention. Similarly, all available data from the control group that was originally randomized will be analyzed as the control group, including any who receive the NMES intervention. Multiple imputation (MI) using the mice package in R will be applied to analyze the missing data.

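### Inclusion criterion 4 makes completing the experimental course a condition of entry, a post-randomisation event that contradicts the protocol's own intention-to-treat rule

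*Protocol article*

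**What the plan says.** The fourth item under Inclusion criteria reads "Participant who voluntarily received this experimental treatment and completed the course of treatment". It follows a separate item requiring signed consent.

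Three other sections fix the timing and who can meet the item:

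- Participant recruitment: "Eligible patients will be randomly divided into the NEMS group or control group by an investigator". Eligibility therefore comes first and allocation second.
- NMES group intervention: "NMES intervention will be performed on the first day of patient enrollment, and the intervention will continue for 7 days".
- Control group intervention: "The control group will not receive NMES treatment". Controls receive routine care and early physiotherapy.

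Data collection and statistical analysis states that "All randomized participants will be included in the analyses", in the arm to which they were allocated. It expressly keeps NMES patients who do not finish the stimulation or never receive it, and it plans multiple imputation for missing values.

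Two further statements bear on the point. The same section has a rule that begins "If participants terminate the trial or deviate from the intervention protocol" and tells investigators to record data from the last intervention and to give the reason for withdrawal. Exclusion criterion 8 is "Death within 24 h", with no stated starting point.

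**The concern.** An eligibility criterion should be decidable before allocation. This one depends on what happens in the week after it, and on a treatment that only one arm is offered. Someone applying the eligibility list could class an NMES patient who stopped early as wrongly enrolled and take that patient out. Someone applying the analysis section must keep the same patient in. The article does not say which governs.

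The stake is bias. Patients who become unstable or cannot tolerate stimulation are plausibly weaker than those who finish. Removing them from the NMES arm, with no matching removal among controls, would raise the NMES mean MRC score even if stimulation did nothing.

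**Working it through.** **1. The passages side by side**

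| Question | Inclusion criterion 4 | Rest of the article |
|---|---|---|
| When is it known? | After the course is finished | Eligibility precedes allocation; the course takes 7 days from enrolment |
| Can a control meet it? | Not literally | Controls get no NMES |
| Is an NMES non-completer in the trial? | Not eligible | Included and analysed as randomised |

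The last row is a direct contradiction. The first two show that the criterion cannot be operated as printed.

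**2. The plan's own sample size, for reference**

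Inputs from the sample-size section: 0.45 versus 0.11, α = 0.05 (taken as two-sided), power 90%, 20% loss. With unpooled variance:

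n = (1.960 + 1.282)² × (0.45×0.55 + 0.11×0.89) / (0.45 − 0.11)² = 10.51 × 0.3454 / 0.1156 = 31.4, so 32 per arm.

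32 / (1 − 0.20) = 40 per arm, 80 in total. This matches the stated figure, and rewording criterion 4 does not change it.

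**3. Size of the bias if non-completers were removed from the NMES arm only**

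The documents give no non-completion rate and no correlation between completion and outcome, so both are assumptions here. Set-up: no true effect, outcome SD 1, 40 controls kept, a fraction q of the 40 NMES patients removed, and a correlation ρ between a latent tendency to complete and the outcome.

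- Shift in the NMES mean: m = ρ × φ(c) / (1 − q), where c is the q-quantile of the standard normal and φ its density.
- Standard error: SE = √(1/40 + 1/[40(1 − q)]), treating the SD after removal as still 1.
- Two-sided type I error ≈ 1 − Φ(1.96 − m/SE) + Φ(−1.96 − m/SE).

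Worked case, q = 0.20 and ρ = 0.5: c = −0.842 and φ(c) = 0.280, so m = 0.5 × 0.280 / 0.80 = 0.175. SE = √(1/40 + 1/32) = 0.237 and m/SE = 0.738. The error is 1 − Φ(1.222) + Φ(−2.698) = 0.111 + 0.003 = 0.114.

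| q removed | ρ | Shift (SD) | Two-sided type I error |
|---|---|---|---|
| 5% | 0.3 | 0.033 | 5.2% |
| 5% | 0.5 | 0.054 | 5.7% |
| 10% | 0.3 | 0.058 | 5.7% |
| 10% | 0.5 | 0.097 | 7.1% |
| 20% | 0.3 | 0.105 | 7.3% |
| 20% | 0.5 | 0.175 | 11.4% |

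**4. If the intention-to-treat text is followed**

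Nobody is removed for non-completion, q = 0, and this source of bias is zero.

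**The case against.** The best defence is that criterion 4 is loose wording for willingness to receive and complete the assigned course. It stands next to the consent item, completion cannot be checked at screening, and the literal reading would empty the control arm, which nobody intends. The analysis section is more specific and expressly keeps non-completers. This is a plausible account of what was meant, and it means that the bias above is conditional. It does not rescue the wording: the criterion describes treatment as already received and completed, consent is already a separate item, and the text does not say that the analysis section overrides it.

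Three stronger readings are tempting but not supported.

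- *That the deviation rule is a second breach of intention-to-treat.* The sentence starting "If participants terminate the trial or deviate from the intervention protocol, the investigators will record the trial data" says what is recorded. It excludes nobody and does not say that follow-up ends. Study design expects everyone to complete data collection and follow-up, and the analysis uses all available data with imputation. Nor is it right that controls have no intervention from which data could be taken, since the article describes one for them. What stands is an ambiguity: the sentence treats deviation like withdrawal and could be read as cutting data off at the last intervention.
- *That* "Death within 24 h" *is another post-randomisation exclusion.* It would be if counted from enrolment, but the article does not say so. Counted from ICU admission it is merely redundant, because inclusion criterion 2 already requires at least 24 h in the ICU.
- *That the false-positive risk is dramatic.* Removing exactly the 8 weakest of 40 NMES patients gives, by simulation of 20,000 trials, a shift of 0.34 SD and about a 35% chance of a significant result favouring NMES, against a nominal 2.5%. That is an extreme case. Its 20% is borrowed from the overall allowance for loss to follow-up, which is not an NMES non-completion rate, and the removal itself runs against the intention-to-treat text.

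**Conclusion.** Criterion 4 is wrong as written. It conditions entry on a post-randomisation event, no control can literally satisfy it, and it contradicts the analysis section. That conclusion comes from the text alone and needs no numerical assumption.

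The size of the consequence does rest on assumptions. With 10–20% removed from the NMES arm only and a correlation of 0.3–0.5, the spurious benefit is about 0.06–0.17 SD and the two-sided type I error about 6–11%. The direction assumes that non-completers are the weaker patients. The illustration does not model deaths, which remove the day-7 MRC score in either arm.

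A reader might infer that the planned analysis is itself a completers' analysis. The documents do not support that: the stated analysis is intention-to-treat and, if followed, is free of this bias. The deviation sentence and exclusion 8 are points to clarify, not further contradictions.

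**What to change.** 1. Reword inclusion criterion 4 as willingness, at consent, to be randomised and to take part in the assigned course, in either arm. State that patients who do not complete it remain eligible and are analysed as randomised. Report completion by arm as adherence.
2. In Data collection and statistical analysis, separate deviation from withdrawal. State that participants in both arms who stop or deviate from the intervention but do not withdraw consent keep the scheduled day-7 and month 1, 3 and 6 assessments.
3. Give exclusion criterion 8 a time origin before randomisation, or drop it as redundant with the 24 h ICU-stay requirement.

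The cost is a wording amendment. The sample size stays at 40 per arm and no visit is added, because these assessments are already in the schedule.

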### Intervention

Two physiotherapists with more than 5 years of clinical experience from the Second Affiliated Hospital of Chongqing Medical University will be responsible for the trial’s intervention. After undergoing standardized operation training, two qualified physiotherapists will administer NMES therapy to the NMES group. Meanwhile, the control group will receive standard usual care only. The intervention will last 7 days.

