### Safety assessment and monitoring

NMES intervention will be carried out strictly based on the instrument operation specifications and implemented by two physiotherapists who have completed operation training. Patients will be informed of the potential adverse events of NMES and sign an informed consent form. Adverse events may occur during treatment: mean arterial blood pressure < 65 mmHg, 40 bpm < heart rate < 130 bpm, SpO_2_ < 88%, skin redness, skin burns, skin blisters, pain, myocardial ischemia, and arrhythmia. The NMES group will complete NMES therapy under the supervision of a physiotherapist. During treatment, any patient discomfort will be dealt with immediately (reduce the intensity of electrical stimulation or stop the intervention). The research team will judge the severity of adverse events and analyze the correlation with the intervention. Patients who suffer harm or complications caused by the intervention will receive medical treatment at the Second Affiliated Hospital of Chongqing Medical University free of charge. All serious adverse events will be reported to the ethics committee within 48 h.

Based on the sequential study design, the primary outcome will be analyzed when 50% of participants (40 participants) have randomly enrolled to complete the intervention and data collection. An independent statistician who is blinded to the intervention process will be responsible for performing the data analysis. Type I error statistical analysis will be performed using the Pocock approach with *α* = 0.05. The interim analysis results will be reported to the data monitoring committee (DMC). The DMC will access all data and discuss to decide whether the trial should be continued, modified, or halted earlier than intended.

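### Inclusion criterion 4 makes receiving and completing the experimental treatment a condition of eligibility, which cannot be judged before randomisation, cannot literally be met by controls treated as planned, and contradicts the intention-to-treat rule

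*Protocol article*

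**What the plan says.** The Inclusion criteria section lists four conditions. The fourth, placed directly after signed consent, is "Participant who voluntarily received this experimental treatment and completed the course of treatment".

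Four other places in the protocol article bear on it:

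- **Participant recruitment** fixes the order of events: "Eligible patients will be randomly divided into the NEMS group or control group by an investigator". Treatment comes after entry: "patients will be given corresponding intervention immediately after participating in the trial".
- **NMES group intervention** gives the timing: "NMES intervention will be performed on the first day of patient enrollment, and the intervention will continue for 7 days".
- **Intervention** and **Control group intervention** say what controls get: "Meanwhile, the control group will receive standard usual care only" and "The control group will not receive NMES treatment".
- **Data collection and statistical analysis** adopts intention to treat for all randomised participants and spells out the NMES arm, "including participants from the NMES group who do not complete the NMES intervention or even do not receive NMES intervention". It also lets participants withdraw at any time.

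The Safety assessment and monitoring section lists, as possible responses to discomfort during a session, "reduce the intensity of electrical stimulation or stop the intervention". Incomplete courses are therefore foreseen as possible.

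**The concern.** An inclusion criterion should be decidable from what is known before allocation. This one is worded in terms of what happens during the week after allocation. Staff working from the text could classify an NMES patient who stopped early as never having been eligible and drop that patient, while the analysis section requires the same patient to be kept.

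What is at stake is who counts in the primary comparison, the MRC score at day 7, in a trial of 80 patients. Patients who complete seven daily sessions are plausibly less sick than those who do not. A completers-only NMES arm set against all controls could look stronger at day 7 without any treatment effect.

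**Working it through.** **1. The statements side by side**

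| Question | Criterion 4 | Elsewhere in the article |
|---|---|---|
| When is it known? | After the course is completed | Eligibility is settled, then randomisation, then a 7-day course |
| Can a control meet it? | Requires the experimental treatment | Controls are assigned usual care without NMES |
| Is an NMES non-completer in the trial? | No, if read literally | Yes, analysed in the NMES group |
| Is an NMES patient who was never treated in the trial? | No, if read literally | Yes, analysed in the NMES group |

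The first two rows show that the criterion cannot work as an entry condition. The last two show a direct contradiction with the analysis rule.

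**2. The plan's own figure**

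The illustration below uses 40 per arm, so that figure was checked first. Inputs from the sample size section are incidences 0.45 and 0.11, α = 0.05 (taken as two-sided) and 90% power. With unpooled variance:

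n = (1.960 + 1.282)² × (0.45 × 0.55 + 0.11 × 0.89) / 0.34² = 31.4, so 32 per group.

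With 20% loss, 32 / 0.80 = 40 per group, 80 in total. The stated size is reproduced. The point about criterion 4 does not depend on it.

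**3. What literal application could do (illustration only)**

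Assumed, because the article gives none of these: no true effect; the criterion removes patients in the NMES arm only; all 40 per arm would have a day-7 MRC score; SD scaled to 1 in each analysed group; a share f does not complete; non-completers score g SD below completers, in either arm.

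- Bias = f × g. The NMES arm holds completers only, while the control mean is lowered by f × g.
- SE = √(1/[40(1 − f)] + 1/40).
- False-positive risk = P(|Z| > 1.96) when Z is shifted by bias/SE.

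| f | g | Bias (SD) | SE | Shift | Two-sided risk |
|---|---|---|---|---|---|
| 20% | 0.5 | 0.10 | √(1/32 + 1/40) = 0.237 | 0.42 | about 7% |
| 20% | 1.0 | 0.20 | 0.237 | 0.84 | about 13% |
| 30% | 1.0 | 0.30 | √(1/28 + 1/40) = 0.246 | 1.22 | about 23% |

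Simulation with a t test (15,000 trials) gave 7.3%, 13.4% and 24.0%.

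**4. The same idea on a binary scale**

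Take an ICU-acquired weakness risk of 0.45 in both arms and 20% non-completion in the NMES arm. If non-completers have a risk of 0.6, 0.8 or 1.0, the completers' risk is (0.45 − 0.20 × risk) / 0.80 = 0.412, 0.362 or 0.312. The spurious benefit is 3.8, 8.8 or 13.8 percentage points. The chance of a significant result favouring NMES is about 5%, 11% or 22%, against a nominal 2.5% in that direction.

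**The case against.** The best defence is that the criterion is a wording slip. The article often uses the past tense for planned work, the sentence follows the consent criterion, and it contains the word for voluntary participation. It most plausibly means willingness to be treated and to complete the course. The recruitment section supports this: investigators check the eligible list daily for completion, so patients are called eligible while completion is still open. The analysis section then states intention to treat in detail, with multiple imputation for missing data, and no section provides for removing a randomised patient as ineligible.

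Much of this stands. It explains the sentence and makes misuse less likely. It does not make the sentence correct, and staff and readers must work from the text.

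The defence also limits the illustration:

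- The article describes both arms as receiving a corresponding intervention. If the criterion means the allocated course, it would act on both arms and the one-arm calculation would not apply.
- The analysis section foresees that some controls may receive NMES, so it is too absolute to say that no control ever could meet the criterion. The accurate statement concerns controls treated as planned.
- Patients who die or leave before day 7 have no day-7 score to remove. Their absence is a missing-data matter that rewording the criterion does not solve.

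**Conclusion.** The criterion is wrong as written. It rests eligibility on events after randomisation, excludes controls on a literal reading, and contradicts the analysis rule. This follows from the text alone and needs no assumption.

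The size of any harm is conditional. Only if the criterion were applied to the NMES arm after randomisation, against the analysis section, would the two-sided false-positive risk be about 7% to 13% (20% non-completion, gap of 0.5 to 1 SD, no true effect). These are not predictions for the trial.

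Four stronger readings might be inferred, and the documents do not support them:

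- **That the criterion overrides intention to treat.** No section gives it precedence, and the analysis section expressly keeps non-completers and non-recipients.
- **That patients stopped for intolerance drop out of the safety denominator.** The safety section defines no such denominator and requires all serious adverse events to be reported.
- **That the plan itself expects 20% non-completion.** Its 20% is loss to follow-up. The 20% used above is an assumption.
- **That the bias can be expressed as a share of the stated effect size of 0.5.** That figure stands beside two proportions, with no MRC standard-deviation scale given.

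**What to change.** Delete inclusion criterion 4. If it was meant to express willingness, replace it with a condition known at screening, for example that the patient agrees to be randomised and to receive the allocated care. Add one sentence stating that no randomised patient is removed for not receiving or not completing the allocated intervention, so that the Inclusion criteria agree with the analysis section.

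The cost is a short protocol amendment. Sample size and procedures do not change. Compared with a completers-only analysis, the effect estimate may be slightly smaller because non-completers stay in, which is what the stated intention-to-treat analysis already implies.
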